## Abstract

**Background:**

The lack of access to physical therapists in developing countries and rural areas poses a significant challenge in supervising postsurgical rehabilitation, potentially impeding desirable outcomes following surgical interventions. For this reason, this study aims to evaluate the feasibility, safety, and effectiveness of utilizing a digital rehabilitation program based on computer vision and augmented reality in comparison with traditional care for patients who will undergo isolated meniscus repair, since to date, there is no literature on this topic.

**Methods:**

This study intends to enroll two groups of participants, each to be provided with informed consent before undergoing randomization into either the experimental or control group. The experimental group will undergo a digital rehabilitation program utilizing computer vision and augmented reality (AR) technology following their surgical procedure, while the control group will receive conventional care, involving in-clinic physical therapy sessions weekly. Both groups will adhere to a standardized rehabilitation protocol over a six-month duration. Follow-up assessments will be conducted at various intervals, including preoperatively, and at 2 weeks, 6 weeks, 12 weeks, and 24 weeks postoperatively. Imaging assessments and return-to-play evaluations will be conducted during the final follow-up. Clinical functionality will be assessed based on improvements in International Knee Documentation Committee (IKDC) and Visual Analog Scale (VAS) scores.

**Registration number:**

ChiCTR2300070582.

## Introduction

The lateral and medial menisci protect articular cartilage by providing shock absorption, distributing load, and lubricating the articular surface. Injury to the meniscus is prevalent among young and athletic individuals, causing biomechanical alterations of the joint, resulting in increased joint contact stress and possibly precipitating early degenerative changes and osteoarthritis [1, 2]. Studies have established that meniscectomy increases the likelihood of accelerated knee osteoarthritis; thus, arthroscopic procedures with suturing or meniscoplasty (central meniscal resection) are usually employed to preserve as much meniscal tissue as possible, depending on the shape of the damaged meniscus [1–4].

Postoperatively, physical therapy plays a pivotal role [5]. However, a significant challenge arises from the limited access to skilled therapists in developing countries and remote rural areas [6–8]. Patients in these resource-constrained regions often face long commutes to healthcare facilities, reduced compliance with rehabilitation protocols, and a lack of monitoring during the postoperative phase [6]. Consequently, recognizing the limitations inherent in conventional clinic-based physical therapy practice, digital rehabilitation programs will emerge as a promising supplemental solution. [7, 9]

Advanced technologies such as augmented reality and computer vision will have the potential to offer interactive digital therapy experiences [10]. Currently, the utilization of the VR system facilitates home-based rehabilitation training and increases its interactivity and enjoyment. [11–15] However, in VR, patients interact with a virtual environment that simulates real-life activities. The risk associated with this technology is that potentially dangerous situations may not be appropriately identified; however, images portrayed in both AR and virtual reality overlap with real-world images, thus allowing patients to be aware of potential dangers. [10] The incorporation of both virtual and real-world elements combined with real-time interaction and standard rehabilitation protocols can be leveraged to promote the recovery of an injured joint [15]. Telerehabilitation using technologies such as computer vision (CV) offers the potential for improving access to rehabilitation programs. The use of markerless human pose estimation based on computer vision in telerehabilitation is a promising research area, as it offers the advantage of closely monitoring movement without the need for external markers to capture motion data [16]. In our study, AR technology will utilize readily available devices such as smartphones, eliminating the need for additional hardware and providing greater convenience, while computer vision will facilitate real-time monitoring of patient movements and exercise postures.

The protocol of the digital rehabilitation program is based on the concept of accelerated rehabilitation after meniscal surgery proposed in 1996, suggesting that early postoperative weight bearing and knee range of motion (ROM) could reduce the risk of joint adhesions and muscle atrophy [5]. In recent years, accelerated rehabilitation programs for early weight bearing and active ROM after meniscus repair have shown positive results in patients with longitudinal meniscus tears [1, 2, 17]. Further research is warranted to investigate the safety and efficacy of early weight bearing and ROM training in patients who undergo complex meniscal tear repair, as the rehabilitation strategies may vary depending on tear pattern. [2, 18]

As a result, this study will utilize computer vision and smartphone-based augmented reality to overcome the limitations associated with conventional postoperative rehabilitation methods, with the goal of enhancing orthopedic postoperative outcomes. This study will involve delivering standardized exercise protocols using a digital platform, providing patients with continuous and effective physical therapy training supplemented by real-time feedback. Notably, there is currently no literature reporting the application of augmented reality and computer vision for postoperative recovery in patients with isolated meniscus injuries.

## Aim of study

This study will recruit adult participants diagnosed with isolated longitudinal meniscus injuries confirmed through arthroscopic examination and scheduled for meniscus repair. The primary objective of this research is to assess the safety, effectiveness, and feasibility of implementing a digital rehabilitation program that incorporates computer vision and augmented reality as part of the postoperative rehabilitation process.

## Methods

### Study design

This is a single-center, prospective, randomized controlled study. After receiving informed consent, participants will be randomly allocated into two groups: the experimental group and the control group will adopt the standardized rehabilitation protocol (Table 1). The experimental group will engage in a digital rehabilitation program that can be completed from home, whereas the control group will attend weekly physical therapy clinic sessions for exercise guidance. The flowchart of the study is shown in Fig. 1.

**Table 1 Tab1:** The standardized postoperative rehabilitation plan

Overall goal: Stage 1: 0–2 weeks: Control of swelling and symptoms after surgery, early progressive weight bearing, and ROM
Control of swelling and symptoms: (1) apply ice at least 3 times a day after surgery, 20 min each time; (2) apply the elastic bandage to compress the affected limb; (3) elevate the affected limb and lie flat on your back when sleeping and cushion a pillow with a certain thickness under the affected limb
ROM and brace use: (1) 0–60 degree fixation, early gentle knee movement under sitting position (2) heel support training, ensuring knee joint at 0 degrees
Weight bearing: The knee brace is secured in the fully extended knee position, and crutches are used to transition from no weight bearing to partial weight bearing as tolerated
Exercises: (1) sitting hamstring pull (2) ankle pump (3) quadriceps isometric training (4) straight leg elevation training (15–30 degrees) (5) hamstring isometric training
Overall goal: Stage 2:3–6 weeks: Early exercise and strength training, ROM, and partial weight bearing as tolerated
ROM and support use: (1) 3–4 weeks: 0–90-degree fixation, complete knee extension and bend to 90 degrees (2) 5–6 weeks 0–120-degree fixation, bend to 120 degrees
Weight bearing: With the knee brace fixed in the fully extended knee position, and using crutches, gradual weight bearing to full weight under tolerable conditions, and gradually remove of the crutches
Exercise: In addition to the training in the previous stage, include: (1) knee shin slide (2) supine straight leg raise 30 to 60 degrees (3) hip outreach training (4) lift heel stand (5) hip outreach (6) hip and (7) seat after knee flexion and stand
Overall goal: Stage 3: Weeks 7–12: Functional regression, gradual reduction of brace use, and restoration of total joint range of motion
ROM and brace use: (1) restore full joint range of motion and (2) gradually stop brace use after full weight bearing
Exercise: Add advanced resistance training: (1) recumbent resistance straight leg raise (2) step-down training (3) heel raise training (4) knee flexion (5) straight leg draft with elastic band (6) recumbent resistance heel slide (7) forward lunge (8) half squat against wall 50 degrees (9) four-point kneeling cross stretch
Overall goal: Stage 4: Weeks 13–24: Early exercise training, full-strength recovery, cardiovascular exercise adaptation, and exercise-specific training (speed and agility training)
Exercise: Continue with the third stage of training and build on this cardiovascular endurance training (power cycling, recovery running, and jumping)
Phase 5: after return to sports assessment to determine whether to return to body contact, rotating sports

**Fig. 1 Fig1:**
[figure not shown]
Research flowchart

### Randomization

SPSS 23.0 (IBM, New York, NY, USA) will be used to generate random numbers. Subjects with odd numbers will be assigned to the experimental group, and subjects with even numbers will be assigned to the control group. The envelope method will be used for hidden grouping, which will be implemented by a third party. The random allocation scheme will be stored in an opaque envelope, which will be opened in succession according to the order of inclusion, thereby determining the assigned group for each patient. After that, the envelopes will be given to the study implementer, who will then use inclusion and exclusion criteria to decide whether each patient can be included in the study.

### Blinding method

For this study, blinding of the interveners and patients was not feasible. Blinding should be applied to the data collectors, data analysts, and outcome assessors in the study.

### Subjects

Inclusion criteria:Isolated meniscus injury diagnosed by magnetic resonance imaging (MRI)Confirmation of a longitudinal tear pattern (including bucket handle tears) under arthroscopy, with a repairable tear.Suture meniscus repair with or without partial meniscectomyParticipants have sustained their meniscus injury due to physical activities, such as playing basketball.Willing to participate in this clinical trial and receive follow-up.

Exclusion criteria:Preoperative MRI diagnosis with other ligament or chondral lesions;A discoid meniscus was diagnosed under arthroscopy.Trauma and surgery to other weight-bearing joints in the lower extremities, such as torn ligaments in the ankle and necrosis of the femoral head in the hip, can indirectly affect knee load and movement.Knee osteoarthritis, defined by Kellgren–Lawrence grade II or higher or Outerbridge classification grade II and above. [19, 20]

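### The ligament exclusion rests on preoperative MRI alone, although the stated population is isolated injury confirmed at arthroscopy

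*Protocol article*

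**What the plan says.** The Aim of study section of the protocol article sets the population as "adult participants diagnosed with isolated longitudinal meniscus injuries confirmed through arthroscopic examination", scheduled for meniscus repair. The Abstract and Introduction also frame the question around isolated meniscus repair and isolated meniscus injury.

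The Subjects section names the examination that governs several of its criteria:

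- The first inclusion criterion makes isolation a finding of magnetic resonance imaging.
- The second uses arthroscopy: "Confirmation of a longitudinal tear pattern (including bucket handle tears) under arthroscopy, with a repairable tear".
- The first exclusion is "Preoperative MRI diagnosis with other ligament or chondral lesions".
- The second exclusion is "A discoid meniscus was diagnosed under arthroscopy".
- The fourth exclusion is "Knee osteoarthritis, defined by Kellgren–Lawrence grade II or higher or Outerbridge classification grade II and above". It does not say by which examination the Outerbridge grade is obtained.

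Under Surgical procedure, surgery is arthroscopic for everyone. Under Randomization, the envelopes are opened in order and then passed to the study implementer, who applies the inclusion and exclusion criteria.

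**The concern.** The Aim and the criteria name different examinations for the same property. The Aim has isolation confirmed at arthroscopy. The criteria have it established on MRI and never revisit it for ligaments, although the joint is inspected in every patient and arthroscopy already decides entry on other grounds.

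The question is whether the enrolled patients are those the trial says it studies. A concomitant ligament lesion could plausibly affect the IKDC, Lysholm and Tegner scores and, in the return-to-play assessment (Table 2), the jump, balance and step-down tests. That is a clinical expectation, not a figure from the protocol. If such knees enter, the results describe a broader group than isolated longitudinal tears, and the outcomes are likely to be somewhat more variable.

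**Working it through.** No figure in the protocol bears on this point, so the check is a reading of the criteria. Take a knee with a repairable longitudinal tear, a preoperative MRI showing no other lesion, and a ligament tear in the same knee seen for the first time at arthroscopy. Assume the patient is otherwise eligible.

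| Criterion (Subjects) | Examination named | Result for this knee |
|---|---|---|
| Inclusion 1: isolated meniscus injury | MRI | Met, because the MRI shows nothing else |
| Inclusion 2: longitudinal, repairable tear | Arthroscopy | Met |
| Inclusion 3: suture repair, with or without partial meniscectomy | None | Met if that operation is done |
| Inclusion 4: injury through physical activity | None | Met by assumption |
| Inclusion 5: willing to take part | None | Met by assumption |
| Exclusion 1: other ligament or chondral lesion | Preoperative MRI | Not triggered |
| Exclusion 2: discoid meniscus | Arthroscopy | Not triggered |
| Exclusion 3: trauma or surgery to other weight-bearing joints | None | Not triggered, because it concerns other joints |
| Exclusion 4: knee osteoarthritis | Kellgren–Lawrence or Outerbridge grade | Not triggered, because it concerns osteoarthritis and cartilage |

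The knee satisfies all five inclusion criteria and triggers none of the four exclusions. It would be enrolled as isolated, yet it does not fit the population in the Aim.

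**Number affected.** This would be the recruited number multiplied by the proportion of MRI-isolated knees that show a ligament lesion at arthroscopy. The protocol gives the first (at most 32 per group) but not the second, so no count follows. One such knee would be 1/32 = 3.1% of an arm, but that holds for any single patient and says nothing about frequency.

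**Sample size.** The 26 per group comes from d = 0.8, alpha 0.05 and power 0.8. A two-sided two-sample t-test with these inputs gives 25.52, rounded up to 26. No eligibility criterion enters this calculation, so rewording one leaves it unchanged.

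**Cartilage.** Any chondral lesion on preoperative MRI excludes, with no grade stated. Separately, "Kellgren–Lawrence grade II or higher or Outerbridge classification grade II and above" excludes as osteoarthritis. Because any one exclusion is enough, no knee is both required and forbidden to enter.

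**The case against.** The strongest reply is that the intent is already clear. The Aim speaks of arthroscopic confirmation, the Abstract of isolated meniscus repair, and the third inclusion criterion describes an operation with no ligament procedure in it. Read together, a knee needing ligament surgery lies outside the described population, and the full protocol may say how unexpected operative findings are handled.

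Part of this stands. The intent can be inferred, and the gap is narrower for a lesion that would itself be operated on. But an aim statement is not a criterion, and the third inclusion criterion does not rule out an additional ligament lesion. Nor is this a detail merely left out of a condensed article: the published list names the examination for the ligament exclusion and limits it to MRI.

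A second reply is that an MRI-missed lesion is a baseline feature, which random allocation spreads over both arms in expectation. That stands in full. A reader might infer a biased treatment comparison, but the wording of this exclusion gives no ground for it.

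A third reply is that another arthroscopic exclusion could do harm. The Randomization section has eligibility decided after the envelopes are opened, so an added exclusion could be applied with allocation known. This also stands, and it makes the timing part of the remedy.

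**Conclusion.** The point holds for ligaments. The Aim and Subjects sections do not agree on how isolation is established, and under the criteria as written a ligament injury first seen at arthroscopy does not exclude. The consequence is a population mismatch and probably some added variability. Neither can be sized from the documents, because no rate of MRI-missed ligament injury is given. The conclusion about the text needs no such rate. The expectation of added variability assumes that a ligament lesion influences knee function outcomes.

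A reader might also infer that the two cartilage exclusions contradict each other. They do not: one concerns concomitant lesions on MRI, the other defines osteoarthritis, and either alone excludes. What remains is that a low-grade lesion reported on MRI may exclude while the same lesion found first by another route may not. Even this assumes that grade I change counts as a chondral lesion under the first exclusion, which the protocol does not say. It is a possible clarification, not an error.

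**What to change.** Extend the ligament part of the first exclusion so that it reads, in substance, *other ligament lesion on preoperative MRI or at arthroscopy*, and keep the exclusion of chondral lesions on MRI as it is. Removing the chondral part would admit knees that are now excluded and would loosen the meaning of isolated.

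Apply the ligament check together with the tear-pattern, repairability and discoid checks, and complete all of them before the allocation envelope is opened. The Randomization section must be changed to match, since it now has the implementer decide eligibility after opening.

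If wanted, the sponsor could add one sentence on how a low-grade cartilage lesion seen only at arthroscopy is handled.

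The cost is the wording of one exclusion criterion and of the sequence under Randomization. No examination is added, because every patient already has the arthroscopy. The downside is a few more intraoperative screening failures. If they occur before allocation, they affect recruitment effort and not the randomised comparison.

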### Sample size

The sample size is calculated based on the calculation method of a pilot study [21], and the effect size is calculated as follows: *d* = 0.8; *α* = 0.05; Power = 0.8. The minimum sample size per group is 26, and the estimated loss of follow-up/exit rate is 20%. Thus, a maximum of 32 participants will be recruited for each group.

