### Outcomes

#### Clinical knee function evaluation

The estimated follow-up time was 1 day before surgery and 2, 6, 12, and 24 weeks after surgery, and the specific evaluation items included knee ROM (2, 6, 12, 24 weeks after surgery), weight-bearing progress (when fully weight bearing) and knee function and pain scores [23] (Lysholm score, Tegner score, IKDC knee subjective function score, and VAS score). At the final follow-up assessment, return-to-play (RTP) status will be evaluated based on the rehabilitation literature available for meniscus repair. **(**Table 2**)**. [4, 24, 25]

**Table 2 Tab2:** Return-to-play assessment

VAS score = 0	
IKDC score > 90	
No active effusion (Brush test negative)	
The difference in circumference between the quadriceps muscles was less than 1.5 cm	
The knee isokinetic strength test showed a ratio of bilateral quadriceps muscles greater than 90%, bilateral hamstrings greater than 90%, and unilateral hamstrings to quadriceps muscle greater than 66%	
Jump test Limb symmetry index (LSI = jump distance on the affected side/jump distance on the healthy side *100%) was greater than 90%, and the test items included a single-leg long jump test and a single-leg triple jump test	
Y-word balance test: bilateral extension asymmetry within 4 cm; bilateral comprehensive score is greater than 90%	
Lateral step-down test showed no dynamic genu valgus	

The clinical function of patients was assessed and evaluated based on IKDC and VAS score improvement via the criteria of minimal clinically important difference (MCID), patient accepted symptom state (PASS), and significant clinical benefit (SCB) [25].According to the study of Gowd et al. [25], the MCID threshold, which represents the minimal clinically important difference, is defined as an improvement of at least 10.6 points in the IKDC score after treatment or intervention. This threshold signifies that a clinically meaningful change in knee joint function is recognized. The SCB threshold, indicating significant clinical benefit, is set at an IKDC score of 27.3 points or higher after treatment or intervention. This threshold is used to confirm that the treatment has brought about a significant clinical benefit. Lastly, the threshold for patient accepted symptom state (PASS) is established at an IKDC score of 57.9 points or higher. This threshold signifies that patients subjectively consider their symptom state to be acceptable.

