## Statistical analysis

Quantitative data will be analyzed using SPSS 21.0 (IBM, New York, NY, USA). The demographic, social, and preclinical characteristics of the subjects in both groups will be described. Differences in these variables between the intervention and control groups will be analyzed using either the Chi-square test or the *T* test, with continuous variables recorded as the mean and standard errors and categorical variables as rates (incidence). For continuous variables, the Shapiro‒Wilk test will be performed to verify that the variables in each group obeyed a normal distribution. For repeated measures, 2-way ANOVA analysis will be conducted. Two independent samples mean comparison *T* tests were used to compare the normally distributed continuous variables between groups. For nonparametric variables, the Kruskal‒Wallis test was used to determine the differences between the groups. Chi-square tests and Fischer exact tests were used to determine differences in categorical variables. Statistical significance was set at *p* < 0.05.

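### The sample size (d = 0.8, 80% power) is tied to no outcome or visit, and no outcome is designated primary, so the stated power and 5% error rate attach to no designated trial conclusion

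*Protocol article*

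**What the plan says.** All references are to the protocol article.

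- **Sample size.** "The sample size is calculated based on the calculation method of a pilot study [21], and the effect size is calculated as follows", followed by d = 0.8, alpha = 0.05 and power = 0.8. The minimum is 26 per group and the assumed loss is 20%. The section ends: "Thus, a maximum of 32 participants will be recruited for each group". It gives no outcome, visit, SD or difference in points.
- **Aim of study.** "The primary objective of this research is to assess the safety, effectiveness, and feasibility of implementing a digital rehabilitation program". Three aims share one primary objective.
- **Outcomes, Clinical knee function evaluation.** The scores are "Lysholm score, Tegner score, IKDC knee subjective function score, and VAS score", followed before surgery and at 2, 6, 12 and 24 weeks. Range of motion, weight-bearing progress and return to play are added. Later sections add imaging and complications.
- **Abstract (Methods) and the same Outcomes section.** Clinical function is judged on improvement in IKDC and VAS. The two are named together; neither is called primary and no visit is fixed.
- **Statistical analysis.** A 2-way ANOVA is planned for repeated measures, and t, Kruskal-Wallis, chi-square and Fisher tests for the rest. The tests are not assigned to outcomes. "Statistical significance was set at" p < 0.05, with no ranking of comparisons.

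**The concern.** A power statement describes one comparison: a given outcome, at a given time, with a given true difference. A 5% error rate likewise describes a designated test, or a designated family of tests. Here neither is identified. Followed as written, the plan would let whichever of several outcomes falls below 0.05 be presented as evidence of effectiveness. It would also let a null result be described as coming from a trial with 80% power, when nobody can say for what.

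The setting makes this more than a formality. Both arms follow the same standardised rehabilitation plan and differ in how it is delivered. Patients cannot be blinded (Blinding method section), and several outcomes are their own reports. Without a primary outcome fixed in advance, a reader of the results cannot separate the planned test from a favourable pick.

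**Working it through.** **1. Reproduce the stated size.** Inputs from the Sample size section: d = 0.8, alpha = 0.05, power = 0.80, equal groups. Sidedness is not stated, so both versions were tried.

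- Normal approximation, two-sided: n = 2(1.960 + 0.842)² / 0.8² = 24.5, so 25 per group.
- Two-sample t test (noncentral t), two-sided: n = 25.52, so 26 per group, with power 0.807 at 26.
- One-sided: 20 (normal approximation) or 21 (t test), which does not give 26.

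The 26 is therefore a two-sided t-test size, and it is correct for its inputs.

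**2. Allowance for loss.** 26 × 1.2 = 31.2, so 32, which matches the plan. Dividing instead gives 26 / 0.8 = 32.5, so 33. With 32 recruited and 20% lost, 32 × 0.8 = 25.6 remain. This gap is negligible and is not part of the point.

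**3. What 26 per group gives if the true difference is smaller.** With the same t test at two-sided 0.05:

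| True d | Power at 26 per group |
|---|---|
| 0.8 | 0.81 |
| 0.7 | 0.70 |
| 0.6 | 0.56 |
| 0.5 | 0.42 |

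Which row applies depends on the outcome and visit, and the article names neither.

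**4. Error rate if any one of several outcomes can count.** For k independent tests, each at 0.05, the chance of at least one false positive is 1 − 0.95^k. For correlated tests it was simulated with equally correlated normal statistics (200,000 runs). The correlations are assumptions, since the article gives none.

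| Tests | Independent | Correlation 0.5 | Correlation 0.8 |
|---|---|---|---|
| 2 (IKDC, VAS, one test each) | 0.098 | 0.091 | 0.078 |
| 4 (four scores, one test each) | 0.185 | 0.156 | 0.114 |
| 16 (four scores at four postoperative visits) | 0.560 | 0.375 | 0.206 |

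The second row is the main figure. It assumes one test per score across visits, as the repeated-measures ANOVA could provide. The third row applies only if the scores are also compared visit by visit.

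**5. Price of keeping several outcomes confirmatory.** With Bonferroni and d = 0.8 for each outcome, two tests (alpha 0.025 each) need 31 per group, and power at 26 is 0.72. Four tests (alpha 0.0125 each) need 37 per group, and power at 26 is 0.62. With one designated primary comparison, 26 evaluable per group stands.

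**The case against.** The strongest reply is that nothing here is miscalculated. A standardised effect needs no SD or points difference to give a sample size, and about 81% power holds for any single continuous comparison with 26 per arm and a true difference of 0.8 SD. The cited pilot study may identify the outcome, and multiplicity methods are commonly left to an analysis plan, which is not shown. All of that stands. The point therefore does not rest on missing multiplicity detail. It rests on the text shown: an Outcomes section and a Sample size section that do not connect, and no designation of which comparison carries the trial's conclusion.

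It is also fair that IKDC and VAS are singled out. That narrows the field to two measures, but still without a visit, a primary label or a link to the sample size.

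Two stronger readings are tempting and are not supported:

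- A reader might infer that every score is tested at every visit. Four scores plus range of motion at four visits would make 20 tests, with a 64% chance of at least one false positive if independent (1 − 0.95^20 = 0.64). The Statistical analysis section does not say this. It assigns repeated measures to a 2-way ANOVA, which could test each score once. The 20-test figure is an upper scenario and not a description of the plan.
- A reader might take 10.6 IKDC points as the protocol's target difference and conclude that the trial is underpowered unless the SD is about 13 points (10.6 / 0.8 = 13.25). The Outcomes section defines 10.6 as an improvement after treatment. It is never offered as a difference between arms, so it cannot be used to judge the power or to read the confidence interval.

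**Conclusion.** The point holds in this limited form. The 26 per group is correct for d = 0.8, two-sided 0.05 and 80% power, but d is attached to no outcome or visit and no outcome is designated primary. The 80% power and 5% error rate are therefore tied to no designated conclusion. If a difference on any of the four scores could count as effectiveness, the false-positive risk is 19% with independent tests and about 11 to 16% at correlations of 0.8 to 0.5. It is higher if scores are also compared visit by visit. These rates assume one test per score and the correlations stated.

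This does not show that the trial is too small. Whether 0.8 SD is realistic cannot be judged until an outcome is named. The text should be changed.

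**What to change.** Before any outcome data are seen:

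1. Designate one primary outcome at one visit, tested between arms at two-sided 0.05. The IKDC subjective score at 24 weeks, the final follow-up, is one candidate. This is a proposal: the article does not favour it over VAS or over another visit, and the sponsor may justify a different choice.
2. Restate the Sample size section to say that 26 evaluable patients per arm give about 80% power for a between-arm difference of 0.8 SD in that outcome. Give the assumed SD and the same difference in points.
3. Make all other outcomes and visits secondary, reported as estimates with 95% confidence intervals and not as stand-alone evidence of effectiveness.

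The cost is protocol wording and a registry update. Secondary p-values lose confirmatory status. No extra patients are needed as long as 0.8 SD can be defended for the chosen outcome. If it cannot, the restated section will make that visible while the target can still be reconsidered.
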